#### Interventions

The family (including all children enrolled at the unit from the same family) will be randomized using stratified randomization by one researcher to one of the groups (intervention vs waiting list). The stratification will be performed considering the dentist will provide the non-face-to-face consultation and the week for inclusion. In this way, balanced randomization was obtained per professional each week.

Randomization order will be generated by the website sealedenvelope.com. The list will be stored under the supervision of the person responsible for randomization ([name]) and the principal investigator ([name]), in cloud storage and on a USB stick. The dentist who will provide the dental care will be unaware of randomization. They will receive the list with families/patients they are supposed to care for each week sent via email by the person in charge of randomization.

The two groups will differ according to the time of application of the intervention and outcome assessment. The non-face-to-face intervention group will receive the intervention immediately after randomization (t0). Then, after two weeks, the outcome will be measured as described further (t2). The waiting list group (control) will not receive the intervention at this time  and then assessed after the same period to permit controlling the answers (t2). Once this is done, the children on the waiting list will receive the intervention regularly (t3) and become part of the previously detailed list of before-and-after study participants. However, for the present RCT, only data without intervention will be considered (t2). The intervention will be provided as described in the before-and-after study *Interventions* section. Both groups will have been contacted by a research team member to explain the study and will have answered a baseline questionnaire previous to randomization (t-2). At this time, all participants will know the teleservice will be available, but they will not know when that will happen.

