#### Sample size and recruitment

The sample calculation was made using the application sample-size.net and considered the primary outcome for the RCT as a reference. As more than one dimension is considered in evaluating the primary outcome, we consider an average between them. A hypothetical user's difference between the perceived and the expected users' quality appraisal related to a regular health service clinic [27] was used to estimate a minimum difference for this trial, aiming at a more conservative calculation. The minimum difference expected was set, then, as 0,17 (effect size) and a standard deviation of 0,53 assumed (based on the worst case scenario in the referred study) [27]. A minimum sample of 306 users or family representatives in the RCT was estimated. Extra 20% was added to compensate for possible losses, resulting in a final sample of 368 families recruited. Thus, the first 368 families from the unit's care list will be included (randomized). To reach the required number of children, all participants registered at the mobile dental care unit will be invited to participate in this study by telephone or social media contact or message, as detailed in the before-and-after study.

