(e) Analysis Plan: The cost-effectiveness strategy will be used for economic analyses. Incremental values will be calculated both for costs and effects. Therefore, the difference between the new strategy and the one you want to replace will be calculated. (ΔE = E_with_tele_ – E_without_tele_ and ΔC = C_with_tele_ – C_without_tele._ The confidence intervals will be estimated, for each parameter, using the bootstrap technique and considering the sample values referring to costs, effects, incremental costs and incremental cost ratio incremental effectiveness.

The decision-making will depend on the interpretation that will be made of the values collected in the cost-effectiveness plane. Depending on the quadrant in which these simulation results are placed, it may be called dominant or dominated, so an incremental-effectiveness cost ratio calculation may be required for the decision to be made. If the results are in the Northeast or Southwest quadrant (Fig. 8), the incremental cost-effectiveness ratio will help to decide whether or not the intervention will be cost-effective, that is, whether the extra expenditure attributed to the strategy is really worth the effect achieved by it, or even, whether what will be saved with the new strategy is worth the loss that has in its effect.

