**Fig. 8 Fig8:**
[figure not shown]
Diagram for interpretation of costs and effects in the cost-effectiveness plan

Acceptability curves will be plotted considering different ceiling ratios. This strategy will be used for each tested effect to check the strategy's cost-effectiveness in different economic evaluations.

(f) Sensitivity analyses: The economic evaluations will initially be evaluated considering a SUS-simulated scenario in which non-face-to-face care is implemented. The confidence limits of the parameters used (effects and costs) will be considered for performing deterministic sensitivity analyses.

We will adopt a Bayesian strategy to probabilistic sensitivity analyses to explore the uncertainties of health effects and costs [32–34]. For this, following the sample distribution, we will create simulations for both effects and costs, using XLSTAT 2021 (Addinsoft, Paris, France) and the effects and incremental costs. Also, the distributions of these parameters will be considered when the probabilistic analyses are performed.

Next, we will also perform other sensitivity analyses, considering the values prospected for the national health system, considering its magnitude and peculiarities. If necessary, subgroup analyses may be adopted to address specific Brazilian regions.

Finally, we will also analyze the expected value of perfect information (EVPI) and budget impact analysis (BIA). The first analysis (EVPI) allows us to know the value attributed to lousy decision-making due to the uncertainties presented in the data when the strategy is incorporated. It also allows us to estimate the value of the information (VOI), allowing the manager to have tangible arguments to decide whether there is interest in searching for evidence for the subject [35]. On the other hand, the BIA is an elemental analysis for planning and dimensioning the expenses inherent to incorporating a new strategy in the health system [36].

Still considering the above scenarios (dental reference unit and SUS), we will use the economic modelling strategy to consider some aspects not directly measurable in the evaluations described above but relevant from the point of view of decision-making. For this purpose, in the model, we will consider the costs and effects (including risks and benefits) inherent to the face-to-face resolution of some complaints and demands that could be resolved in the clinical studies described above.

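### The plan sets a bootstrap confidence interval for the incremental cost-effectiveness ratio with no condition on where the replicates fall; limits of that ratio cannot be read when a material share lies on each side of zero effect

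*Protocol article*

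**What the plan says.** In the protocol article, section Economic and social impact assessment, paragraph (e) Analysis Plan, incremental costs and effects are defined as differences between care with and without teleservice. The paragraph continues: "The confidence intervals will be estimated, for each parameter, using the bootstrap technique", and then "considering the sample values referring to costs, effects, incremental costs and incremental cost ratio incremental effectiveness". Incremental costs have their own place in that list, so the final item is most naturally the incremental cost-effectiveness ratio. Nothing limits when its interval is to be produced.

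The next part of (e) reads the simulation results by quadrant of the cost-effectiveness plane. It brings in the ratio for the decision only in the north-east and south-west quadrants. The text that follows adds acceptability curves for each tested effect. Paragraph (f), Sensitivity analyses, adds probabilistic sensitivity analysis, the expected value of perfect information (EVPI) and a budget impact analysis. It also states: "The confidence limits of the parameters used (effects and costs) will be considered for performing deterministic sensitivity analyses". An interval for incremental net benefit is not mentioned.

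**The concern.** A ratio of incremental cost to incremental effect does not run from good to bad. A negative value arises when teleservice is cheaper and better, and also when it is dearer and worse. A positive value arises in the north-east quadrant, where a high ratio is unfavourable, and in the south-west quadrant, where it is favourable. The ratio also jumps between large positive and large negative values as the effect passes through zero. If enough replicates fall on each side of zero effect, sorting the ratios and taking limits mixes these cases.

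What is at stake is one reported output. A negative lower limit could be read as possible cost saving when the replicates behind it cost more and did worse.

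**Working it through.** **Inputs.** From the RCT's Sample size and recruitment section: "The minimum difference expected was set, then, as 0,17 (effect size) and a standard deviation of 0,53 assumed"; an evaluable total of 306; and, for losses, "Extra 20% was added to compensate for possible losses, resulting in a final sample of 368 families recruited". Equal arms are inferred from the Interventions section ("In this way, balanced randomization was obtained per professional each week"). Alpha, sidedness and power are not stated; two-sided 5% and 80% are assumed.

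**Reproducing the plan's own figure.** n per arm = 2 × (1.960 + 0.842)² × (0.53/0.17)² = 2 × 7.849 × 9.720 = 152.6, so 153 per arm and 306 in total, as stated. Of the variants tried (one- or two-sided; 80%, 85% or 90% power), only two-sided 80% gives 306. The loss allowance is 306 × 1.2 = 367.2, taken up to 368.

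**How often the effect interval includes zero.** SE = 0.53 × √(2/n per arm). The probability is Φ(1.96 − δ/SE), the other tail being negligible. When this happens, more than 2.5% of bootstrap replicates lie on the side of zero opposite to the estimate.

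| Evaluable families | True difference δ | SE | δ/SE | Interval includes zero |
|---|---|---|---|---|
| 306 | 0.17 | 0.0606 | 2.81 | 19.9% |
| 368 | 0.17 | 0.0553 | 3.08 | 13.2% |
| 306 | 0.12 | 0.0606 | 1.98 | 49% |
| 306 | 0.085 | 0.0606 | 1.40 | 71% |

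A direct bootstrap simulation (400 trials, 1,000 replicates each) gave 17.5% for the first row and 11.75% for the second. Both agree with the formula within simulation error.

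This is not the chance that any replicate at all crosses zero. With 306 families and δ = 0.17, at least one replicate falls on each side in 66% of trials with 1,000 replicates and in 84% with 10,000. A handful of crossings does not spoil 95% limits; a share above about 2.5% does.

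**Illustration.** Assume a cost difference of 20 with SE 4, independent of the effect, and percentile limits. The documents give no cost figures and name no type of bootstrap interval, so these are assumptions.

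| Observed effect, in SEs from zero | Replicates below zero | Percentile limits of the ratio |
|---|---|---|
| 1.5 | 6.5% | −1367 to 1888 |
| 1.96 | 2.5% | −174 to 1044 |
| 2.8 | 0.2% | 56 to 389 |

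In the first row the cost difference is five standard errors above zero, so practically no replicate saves money. The negative limit comes from replicates that cost more and do worse. In the last row the limits can be read normally.

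**The same case as net benefit.** At an assumed ceiling ratio of 500, the observed effect is 1.5 × 0.0606 = 0.0909. Net benefit is 500 × 0.0909 − 20 = 25.4, with SE √((500 × 0.0606)² + 4²) = √(918 + 16) = 30.6. The 95% interval is 25.4 ± 59.9, or about −34 to 85. It has a clear order and shows plainly that the data do not settle the question at that ceiling ratio.

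**The case against.** The strongest reply is that the plan already has the right tools. It reads the simulation results, not merely a point estimate, by quadrant. It plots acceptability curves and computes EVPI, both of which work from net benefit at stated ceiling ratios. Paragraph (f) carries forward the limits of effects and costs only, so no later step uses the ratio's interval. All of this stands, and it makes the matter minor. None of it changes the ratio interval that paragraph (e) says will be estimated.

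It is also fair that the wording is garbled, that no interval type is named, and that an article may leave reporting detail to a fuller health-economics plan. The percentile method is an assumption here. But the article does fix the choice to estimate an interval for each listed parameter, and the lack of order across quadrants affects any pair of limits taken from the sorted ratios.

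The figures do not carry over to all the economic work. Three evaluations use different effects and only SERVQUAL has a planned size. Costs are analysed per child whereas the sample is counted in families, and the evaluations start from a simulated health-system scenario. That also stands, so the 20% and 13% belong to the SERVQUAL effect alone.

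A reader might go further and infer that the ratio should never have an interval. The documents and the arithmetic do not support that: when the replicates lie essentially in one quadrant, as in the last row of the illustration, the interval is informative.

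**Conclusion.** The point holds as a minor correction to the analysis. As written, the plan would produce an interval for the ratio even when the replicates spread materially over both sides of zero effect, and such an interval cannot be interpreted. For the SERVQUAL effect at its planned size this arises in about one trial in five with 306 evaluable families and about one in eight with 368, and more often if the true effect is smaller. These figures assume two-sided 5%, equal arms, approximate normality and families as the unit. For the other evaluations the frequency cannot be computed from the document.

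A reader might infer that the economic conclusions or the adoption decision would be invalid. That does not follow, because the decision runs through the plane, the acceptability curves and EVPI. The risk is a misleading reported interval.

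**What to change.** In paragraph (e), state that bootstrap 95% intervals will be given for incremental cost, incremental effect and incremental net benefit (ceiling ratio × effect difference − cost difference), over the ceiling ratios already needed for the acceptability curves. Report the share of replicates in each quadrant. Give an interval for the ratio only when the replicates lie essentially in one quadrant and, as a minimum condition, the 95% interval for the incremental effect excludes zero; otherwise omit it. Reword the garbled list item so that the ratio is named clearly.

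The same replicates serve for everything, and no new data or change in sample size is needed. The only cost is slightly more reporting.

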**Fig. 8 Fig8:**
[figure not shown]
Diagram for interpretation of costs and effects in the cost-effectiveness plan

Acceptability curves will be plotted considering different ceiling ratios. This strategy will be used for each tested effect to check the strategy's cost-effectiveness in different economic evaluations.

(f) Sensitivity analyses: The economic evaluations will initially be evaluated considering a SUS-simulated scenario in which non-face-to-face care is implemented. The confidence limits of the parameters used (effects and costs) will be considered for performing deterministic sensitivity analyses.

We will adopt a Bayesian strategy to probabilistic sensitivity analyses to explore the uncertainties of health effects and costs [32–34]. For this, following the sample distribution, we will create simulations for both effects and costs, using XLSTAT 2021 (Addinsoft, Paris, France) and the effects and incremental costs. Also, the distributions of these parameters will be considered when the probabilistic analyses are performed.

Next, we will also perform other sensitivity analyses, considering the values prospected for the national health system, considering its magnitude and peculiarities. If necessary, subgroup analyses may be adopted to address specific Brazilian regions.

Finally, we will also analyze the expected value of perfect information (EVPI) and budget impact analysis (BIA). The first analysis (EVPI) allows us to know the value attributed to lousy decision-making due to the uncertainties presented in the data when the strategy is incorporated. It also allows us to estimate the value of the information (VOI), allowing the manager to have tangible arguments to decide whether there is interest in searching for evidence for the subject [35]. On the other hand, the BIA is an elemental analysis for planning and dimensioning the expenses inherent to incorporating a new strategy in the health system [36].

Still considering the above scenarios (dental reference unit and SUS), we will use the economic modelling strategy to consider some aspects not directly measurable in the evaluations described above but relevant from the point of view of decision-making. For this purpose, in the model, we will consider the costs and effects (including risks and benefits) inherent to the face-to-face resolution of some complaints and demands that could be resolved in the clinical studies described above.

To construct and validate these models, a group of experts, including experts in economic assessments, in evidence-based practice, service representatives and managers/decision-makers will be involved. The values related to the probability of occurrence of the different effects considered, as well as the costs derived from each of the situations or states included in the decision tree, will be obtained from the clinical studies conducted in the format of face-to-face care and also official data sources or pertinent bibliography. If necessary, data compilation will be done in meta-analysis format for a more robust estimate. Once this is done, the same analytical strategies previously scored will be employed.

Suppose a potential positive effect of the technology applied to primary dental care for children is detected. Then, models to understand how these tools could be used in the post-pandemic period to optimize the care and demand of this type of care within the SUS. For this, new decision trees will be proposed considering for each type of relevant demand (reception, guidance, resolution of some complaints without face-to-face need), possibilities of evolution, leading to inherent effects and costs. Then, another economic evaluation considering the economic impact of maintaining these technological tools within the context of primary care in the SUS in the post-pandemic period may be carried out. Such models may consider values related to the family's need for going to a dental unit for being cared for, caregivers' productivity losses because they accompany children in some visits, increase of dentist's productivity, possible losses due to difficulties in access and technological domain, among other possible points raised in clinical studies and also by the experts involved in the construction of the theoretical framework and validation of the models.

For the proposed frameworks, Markov models will be used, constructed and rotated in the appropriate software TreeAge. Annual cycles will be established and, a priori, a 10-year time horizon will be considered. The base case and health states will also be defined, given what was observed in previous studies. In these models, we will try to contemplate quantitative aspects (size of the population of children in the age group covered by the system) and qualitative (regional specificities) characteristics of the SUS. Exploratory analyses will be made considering possible variations in time horizons.

To verify if the insertion of technologies in primary dental care will impact social inequalities, we will analyze how some parameters associated with access may influence studied outcomes. Participants will be divided into groups considering socioeconomic factors, such as income, maternal education. Further, we will test if there are differences, for example, regarding the difficulties of access to technologies for care and guidance in primary care between these groups. We will collect pertinent data from the clinical studies and consider the mathematically simulated data for prospecting the reality to the national health system.

We will use managed entry agreement schemes to deal with the risk of heterogeneity of findings in economic analyses [37] adapted to the Brazilian reality. At this stage, we will consider the models and decision tress built to check the efficiency of resource allocation when implementing technologies in the management of relevant situations in the face of the COVID-19 pandemic and possible subsequent implementation in the SUS. The risks of uncertainty will be quantified using an instrument proposed for this purpose [38], and its actual impact can be evidenced for the health system managers, for example. That will also be a way to compare the different strategies in different environments (settings) to be incorporated within the national public health system.

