The following specific objectives are defined:To identify the repressed demand for the outage of dental care and the benefits and difficulties, as well as the perception of users, in the implementation of new strategies of non-face-to-face care based on technology (teleservice), using a primary care cell unit for children and prospecting, through models, this situation for the scenario of the Unified Health System (SUS).Perform different forms of economic evaluation to measure whether the gains achieved with the implementation of teleservice (telescreening, teleorientation and telemonitoring) compensate for the additional costs possibly associated with it, or whether they are associated with a long-term resource savings, considering the implementation  dimensioned for the Brazilian public health system.Explore how the introduction of these technologies could benefit the SUS in the trans and post-pandemic period, contribute to the correction of possible inequities in the health care and other social aspects, as well as result in possible differences when different Brazilian scenarios are explored.

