#### Outcomes

As the primary outcome for this before-and-after study, we consider problem-solving, considering the participant as the measurement unit. We will consider all the complaints pointed out by patients and their families during the baseline consultation. To measure that, a 2-weeks-later interview using the same platform (V4H) will address aspects relevant to understanding if the patients' and families' demands are solved during this time. A checklist to identify possible barriers and facilitators related to each type of complaint will be employed on these interviews. The time to resolution of the complaint will be computed as a secondary outcome.

Children will also be asked to toothbrush and floss during this assessment consultation. An external assessor will check the problem-solving related to the demand for oral hygiene orientations. The guidelines for orientation will be used as the reference standard to check if the demand was solved. If the child fulfils all oriented aspects, the demand is fully solved. If at least one assessment criterion is fulfilled, it is considered a partially solved demand. Cases of non-compliance with intervention sessions or those families that give up the consultations were also considered to understand the studied service's implementation.

Other outcomes will be assessed as secondary ones. The teleservice platform will measure consultation time. Technological and non-technological difficulties during the consultation (absences or delays, non-compliance, difficulties in using the platform, accessing the internet or even the computer or mobile phone) will be registered by an external assessor in a specific file at the end of the online session. The caregivers' and child's perceptions on the use of technologies in primary dental care will be collected by specific questionnaire [21] in the two-week-later assessment.

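### The social-inequality analysis aims at a change caused by teleservice, but the only comparison it states is between socioeconomic groups, with no contrast of the gap with and without teleservice

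*Protocol article*

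**What the plan says.** The third specific objective in the Background includes exploring how these technologies could "contribute to the correction of possible inequities in the health care and other social aspects". The last part of the section on economic and social impact assessment gives the aim: "To verify if the insertion of technologies in primary dental care will impact social inequalities". It then names two steps.

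- Association: "we will analyze how some parameters associated with access may influence studied outcomes".
- Group comparison: "Participants will be divided into groups considering socioeconomic factors, such as income, maternal education", and then "we will test if there are differences, for example, regarding the difficulties of access to technologies for care and guidance in primary care" between those groups.

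On data it adds: "We will collect pertinent data from the clinical studies and consider the mathematically simulated data for prospecting the reality to the national health system".

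The Outcomes section of the before-and-after study has an assessor record, at the end of the online session, "Technological and non-technological difficulties during the consultation". In the RCT, families are randomised to immediate teleservice or to a waiting list, and SERVQUAL is measured in both arms at t2, before the waiting-list arm receives teleservice. The RCT statistical methods allow an optional regression on variables besides the group. They state no interaction between group and socioeconomic position.

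**The concern.** Impact on inequality means that the gap between better-off and worse-off families differs according to whether teleservice is present. The stated test asks whether there is a gap. The two questions can have opposite answers: a gap may exist that teleservice did not cause, and no gap may remain because teleservice removed it. The second case is the benefit named in the objectives. The Discussion raises both possibilities, better equity and new disparities from digital difficulty, so the direction of change is what a policy reader will want. The economic analysis plan defines incremental effects and costs as with minus without teleservice. The inequality paragraph states no such contrast.

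**Working it through.** **1. Question against test.** Let g1 be the socioeconomic gap in an outcome with teleservice and g0 the gap without it.

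- Stated aim: is g1 − g0 different from 0?
- Stated test, applied to families who had teleservice: is g1 different from 0?
- Stated test, applied to both RCT arms pooled (equal arms, same strata split): is (g0 + g1)/2 different from 0?

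Neither form of the test estimates g1 − g0.

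**2. Two kinds of outcome.** Technology difficulties are recorded at the teleconsultation, so g0 is undefined and g1 simply describes a digital divide. SERVQUAL is measured in both arms at t2, so g0 and g1 both exist and their difference can be estimated.

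**3. The plan's own sample size.** Inputs from the RCT sample size section: difference 0.17, SD 0.53. Alpha and power are not given there; two-sided 0.05 and 80% are assumed because they reproduce the figure.

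n per arm = 2 × (1.960 + 0.842)² × 0.53² / 0.17² = 152.6, so 153 per arm and 306 in total. Then 306 × 1.2 = 367.2, so 368. Both figures reproduce.

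**4. Unchanged gap (g1 = g0) in an outcome that exists without teleservice.** The size of the gap and the equal strata are assumptions. Normal approximation, two-sided 5%.

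- 184 teleservice families, 92 per stratum, gap 0.3 SD: z = 0.3 / √(2/92) = 2.03; probability of significance about 53% (52% by simulation with a t-test).
- 153 teleservice families, 76.5 per stratum, SD 0.53: SE = 0.53 × √(2/76.5) = 0.0857. A gap of 0.17 gives z = 1.98, about 51%. A gap of 0.10 gives about 22%, and 0.25 about 83%.

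The true change in the gap is zero in all of these.

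**5. Closed gap (g1 = 0, g0 > 0).** The comparison among teleservice families rejects in 5% of trials, whatever g0 was.

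**6. What the interaction can deliver.** With a families per arm and share s in the lower stratum:

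SE(g1 − g0) = SD × √(2/(a·s) + 2/(a·(1 − s)))

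For a = 153 and s = 0.5: SE = 0.53 × √(4/76.5) = 0.121. For a change in the gap of 0.17, z = 1.40 and power is 29%.

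| Families analysed | s | Power for a 0.17 change in gap | Change detectable with 80% power |
|---|---|---|---|
| 306 | 0.5 | 29% | 0.34 |
| 306 | 0.3 | 25% | 0.37 |
| 306 | 0.2 | 20% | 0.42 |
| 368 | 0.5 | 34% | 0.31 |
| 368 | 0.3 | 29% | 0.34 |
| 368 | 0.2 | 23% | 0.39 |

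Power of 80% for a change of 0.17 would need about 1,222 families in total at s = 0.5, 1,454 at 0.3 and 1,908 at 0.2.

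**The case against.** The paragraph is short and open. It speaks of participants rather than teleservice users, offers technology difficulties only as an example, and draws on the clinical studies in general, which include the RCT. Inequalities are placed among secondary, exploratory analyses, and model terms are often left to a fuller plan. One figure that lists possible subgroup analyses is not shown. A gradient in technology difficulties can arise only once care is delivered by technology, so for that outcome a group comparison is relevant.

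Much of this stands. A reader might infer that the test is confined to teleservice users; the text does not say so. A reader might also apply the roughly 50% figure to the planned comparison of technology difficulties. That would be wrong, because an unchanged gap with and without teleservice cannot occur for an outcome that does not exist without it. Nor does any rule in the document say that a gradient would be reported as harm done by technology.

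The open wording leaves the choice of outcome free but does not supply the missing contrast: the only comparison stated is between socioeconomic groups, and pooling the arms does not change that. The interaction's low power is a reason to report an estimate with its interval, not to answer a different question.

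**Conclusion.** The point holds as a mismatch between a stated aim and the comparison stated for it, in a secondary analysis. It does not touch the primary outcomes. For technology difficulties the comparison is sound as description but says nothing on net impact or correction of inequity. For outcomes such as SERVQUAL it can be significant when teleservice changed nothing (about half of trials for an unchanged 0.3 SD gradient with 184 families) and null when teleservice closed a gap. Those rates rest on assumed gradients and equal strata; the mismatch itself does not.

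It would go too far to say that the trial cannot address equity. The randomised waiting list allows it for outcomes measured in both arms, though imprecisely.

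**What to change.** In the inequality paragraph, add an exploratory arm-by-socioeconomic-group interaction (income, maternal education) on SERVQUAL at t2 in the RCT. Report the gap in each arm and the difference of the two gaps with a 95% CI.

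State two limits next to it. Precision is low: about 29% power with 306 families, or 34% with 368, for a 0.17 change in the gap with SD 0.53 and equal strata, and less with unequal strata. And SERVQUAL covers perceived service quality only, not access or oral health.

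Keep the comparison of technology difficulties, labelled as a description of the digital divide among those offered teleservice and not as evidence that inequality changed.

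The cost is one model term and a few sentences. The waiting list, t2 SERVQUAL in both arms and socioeconomic data are already planned. One practical point: caregiver education is listed among variables collected alongside the teleconsultation, which the control arm reaches only after t2, so the grouping variables should come from dental records or the baseline contact where possible. The price is a probably wide interval.
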